#### 2.11.3. Statistical Analysis

Categorical variables will be presented as relative frequencies (%) and continuous variables as mean values (standard deviation) for those normally distributed and as median (interquartile range) for those not normally distributed. Normality will be evaluated graphically (i.e., using histograms, p-p plots, boxplots, q-q plots) and statistically through the Kolmogorov Smirnoff test. Student’s *t*-test will be used to examine differences in all quantitative variables and chi-squared test for all categorical variables between the two intervention groups (NICE vs. MED-LFD). Paired analysis will be utilized to compare all scores between baseline, first follow-up and second follow-up, independently, and also a test-for-trend will be performed to assess any potential longitudinal changes. For the data analysis, the statistical package STATA 16 will be used, and a *p*-value of ≤0.05 will be regarded as statistically significant.

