## 2. Materials and Methods

### 2.1. Eligibility Criteria

Patients 18–65 years of age living in Greece who present with IBS symptoms will be assessed for fulfillment of the Rome IV diagnostic criteria for IBS diagnosis. Patients with Bristol Stool Form Scale (BSFS) types 3–7 with moderate to severe symptoms measured with IBS severity scoring system (IBS-SSS) > 175 will be enrolled. Full blood count, C reactive protein (CRP) or erythrocyte sedimentation rate (ESR), serum thyroid-stimulating hormone (TSH) within normal levels, negative results for tissue transglutaminase (tTg), immunoglobulin A or G antibodies (IgA or IgG) and negative fecal calprotectin are prerequisites for eligibility in the study. Participants > 50 years old should have completed colorectal cancer screening before enrollment.

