### 2.10. Study Endpoints

The study’s primary endpoint is the change from baseline of IBS-SSS at the first and the second follow-up. The co-primary endpoint is the rate of responders for each dietary intervention, defined by a ≥50-point reduction in IBS-SSS, which has been shown to be a clinically significant improvement [21,37], at the first and second follow-ups. Secondary endpoints measured at both follow-ups will include the rate of subjects reporting AR and changes in IBS-QoL, SF-12, HADS, and GSRS-IBS. Adherence to dietary intervention, use of rescue medications, rate of participants who achieve IBS-SSS < 175, discontinuation rate (and causes), and AE/SAEs comprise also secondary endpoints.

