### 2.11. Statistics

#### 2.11.1. Sample Size Calculation

The sample size was calculated at 108 participants (54 per group) with expected values taken from the meta-analysis of Varju et al. [38] and a pre-specified statistical power of 80%, significance level α = 0.05, and 10% adjustment for non-adherence to detect a significant improvement in the primary outcome measure 100 vs. 59 points (estimated standard deviation = 60) in the MED-LFD and NICE groups, respectively.

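### The primary between-arm comparison is an unadjusted t-test on IBS-SSS change; adjusting for the baseline score already collected would protect against chance imbalance and can narrow the interval at almost no cost

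*Protocol article*

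**What the plan says.** Section 2.10 of the protocol article states that the "primary endpoint is the change from baseline of IBS-SSS at the first and the second follow-up". Section 2.11.3 assigns one between-arm test to every continuous outcome: Student's t-test "will be used to examine differences in all quantitative variables and chi-squared test for all categorical variables between the two intervention groups". Read together, these make the primary comparison a t-test on the change score. The article names no baseline covariate, ANCOVA, regression or mixed model.

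The same section adds: "Paired analysis will be utilized to compare all scores between baseline, first follow-up and second follow-up, independently". It also plans a test for trend.

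Three other places bear on the point:
- Section 2.1 selects patients on the outcome scale itself: patients with moderate to severe symptoms and "IBS severity scoring system (IBS-SSS) > 175 will be enrolled".
- Section 2.4.1 describes 1:1 allocation in blocks of four and does not mention stratification.
- Section 2.11.1 sizes the trial on an improvement of "100 vs. 59 points (estimated standard deviation = 60) in the MED-LFD and NICE groups, respectively".

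**The concern.** A change score does use the baseline value, but as if each extra point at baseline carried through to a full extra point at follow-up. Symptom scores usually carry through less than that. The change score then subtracts too much baseline, with two consequences.

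First, the estimate is noisier than it needs to be. Second, if one arm happens to start with worse scores, it will seem to have improved more, whichever diet it received. The test is right on average over all possible randomisations, but the sponsor will have only one, and any imbalance in it will be visible in the baseline table.

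The paired tests raise a smaller, related matter. They do not compare the diets. Because entry requires a score above 175, later scores are expected to fall in both arms through regression to the mean alone. A small p-value from such a test is therefore not evidence that a diet works.

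**Working it through.** **Inputs from the article.** Planned difference 100 − 59 = 41 points and SD 60, read here as the SD of the change (Section 2.11.1). The same section gives "a pre-specified statistical power of 80%, significance level α = 0.05, and 10% adjustment for non-adherence" and 108 participants, 54 per group. A two-sided test is assumed, since the article does not state sidedness. A 10% loss leaves 54 × 0.9 = 48.6, taken as 48 per arm.

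**Inputs not in the article (assumed).** The baseline-to-follow-up correlation rho, from 0.3 to 0.7, and k = follow-up SD / baseline SD, from 1.0 to 1.4. Values of k above 1 are plausible because baseline is cut off at 175 and follow-up is not.

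**1. The plan's own figure.** n per arm = 2 × (1.960 + 0.842)² × 60² / 41² = 33.6, so 34; with the 10% allowance, 34 / 0.9 = 37.8, so 38. The stated 54 is not reproduced. That is a separate issue, and nothing here depends on it. What matters is the power of the unadjusted test at the planned size:
- 54 per arm: SE = 60 × √(2/54) = 11.55; 41/11.55 − 1.96 = 1.59; power 94.4% (94.0% by exact t).
- 48 per arm: SE = 60 × √(2/48) = 12.25; 41/12.25 − 1.96 = 1.39; power 91.7% (91.2% by exact t).

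**2. Precision.** With baseline SD s, Var(change) = s²(1 + k² − 2·rho·k) and Var(ANCOVA) = s²k²(1 − rho²). The ratio is k²(1 − rho²) / (1 + k² − 2·rho·k), which becomes (1 + rho)/2 when k = 1.

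| k | rho 0.3 | rho 0.5 | rho 0.7 |
|---|---|---|---|
| 1.0 | 0.65 | 0.75 | 0.85 |
| 1.2 | 0.76 | 0.87 | 0.97 |
| 1.4 | 0.84 | 0.94 | 1.00 |

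Example (k = 1.2, rho = 0.5): 1.44 × 0.75 / (2.44 − 1.20) = 1.08/1.24 = 0.87.

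Interval width scales with the square root of the ratio. At 48 per arm the 95% half-width for the t-test is about 1.96 × 12.25 = 24.0 points. Under ANCOVA it lies between 24.0 × √0.65 = 19.4 and 24.0 × √1.00 = 24.0. At k = 1, the difference detectable with 80% power falls from 34.3 points to 27.7, 29.7 or 31.6 for rho 0.3, 0.5 or 0.7.

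**3. Shift given a chance imbalance.** The true baseline slope is rho·k, so an imbalance D moves the change-score difference by (1 − rho·k) × D towards the arm that starts worse. With rho = 0.5, 48 per arm and change SD 60, baseline SD = 60 / √(1 + k² − k):

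| k | Baseline SD | SE of baseline difference | Shift at D = 20 | 20 points in SEs | Chance of at least 20 points, either direction | Shift at 1 SE |
|---|---|---|---|---|---|---|
| 1.0 | 60.0 | 12.2 | 10 | 1.6 | about 10% | 6.1 |
| 1.2 | 53.9 | 11.0 | 8 | 1.8 | about 7% | 4.4 |
| 1.4 | 48.0 | 9.8 | 6 | 2.0 | about 4% | 2.9 |

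**4. Simulation check (k = 1, 48 per arm, 20,000 trials at each rho).**
- Overall type I error: 4.9% to 5.0% for the t-test; 4.8% to 5.3% for ANCOVA.
- Power for 41 points: 0.91 for the t-test; 0.98, 0.97 and 0.95 for ANCOVA at rho 0.3, 0.5 and 0.7.
- Type I error among trials where one given arm starts worse by more than one SE: 10.6%, 9.3% and 7.6% for the t-test; 5.5%, 5.0% and 4.6% for ANCOVA.

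**The case against.** The strongest reply is that nothing here is an error. A t-test on change is an unbiased comparison of randomised arms, and the simulation shows that it keeps its overall type I error. Power is already above 90% on the sponsor's own inputs, so the extra precision would rarely alter the result. All of this stands.

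The size of the gain also rests on quantities that the article does not give. The most favourable figures need equal variances at baseline and follow-up, which the entry cut-off makes doubtful. At k = 1.4 and rho = 0.7 the slope is 0.98 and ANCOVA gains essentially nothing. That stands too, and is why a range is given. Across this range, however, ANCOVA is not materially worse.

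It may be said that covariates belong in an analysis plan that is not shown. This does not answer the point, because the article does not leave the method open: it names the test and applies it to all quantitative variables.

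A reader might infer that the baseline score is thrown away, or that regression to the mean biases the comparison of diets. Neither follows. The change score uses baseline with a fixed slope, and regression to the mean is equal in expectation in the two arms. A reader might also infer that allocation is known to be unstratified, or that the sponsor means to claim efficacy from the paired tests. The article is silent on stratification, and it specifies a separate between-arm test.

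**Conclusion.** The point holds as a worthwhile improvement to the primary analysis, not as a flaw that invalidates it. The planned test is sound on average, but it is less precise than it could be and exposed to whatever baseline imbalance the single randomisation produces.

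Over the assumed ranges, adjustment removes between none and about a third of the variance. A plausible but uncommon 20-point imbalance would shift the unadjusted estimate by 15% to 24% of the planned difference (6/41 to 10/41). These figures assume a linear baseline relation with the same slope in both arms, and SD 60 as the SD of change.

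On the paired tests, only a caution is supported: they do not compare diets, and entry on a high score means that part of any fall is expected without a diet effect.

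**What to change.** In Section 2.11.3, replace the t-test for IBS-SSS change with ANCOVA at each follow-up, with arm and baseline IBS-SSS in the model, and report the adjusted difference with its 95% confidence interval. Do the same for IBS-QoL, SF-12, HADS and GSRS-IBS, each with its own baseline. Separate models fit the design better than a mixed model with a common time factor, because Section 2.9 sets the first follow-up at different times in the two arms and Section 2.10 names no single primary timepoint.

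Add one sentence saying that the paired tests are descriptive and are not evidence of a diet effect, because entry requires IBS-SSS above 175 and scores are expected to fall in both arms.

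The cost is one degree of freedom per model and a change of wording; the baseline scores are already collected. Fix it before outcome data are seen, so that the covariate cannot look data-driven. The change does not repair the per-protocol-only analysis of IBS-SSS change (Section 2.11.2) or the unequal timing of the first follow-up, which need their own answers.

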#### 2.8.3. Adherence

Adherence to the diets will be assessed weekly by telephone, by asking the question: “How often did you follow your weekly diet?” and scored on a 5-point Likert scale (never, rarely, sometimes, most of the time, and every day).

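### The chi-squared rule for all categorical variables ignores the order of the five-level adherence scale; the power cost is conditional, about 17 to 24 points for moderate one-directional shifts and less elsewhere

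*Protocol article*

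**What the plan says.** Section 2.8.3: "Adherence to the diets will be assessed weekly by telephone", with the answer "scored on a 5-point Likert scale (never, rarely, sometimes, most of the time, and every day"). The labels carry no numeric codes, and no rule is given for combining the weeks.

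Section 2.10 makes adherence a secondary endpoint, in a list that opens with "Adherence to dietary intervention, use of rescue medications, rate of participants who achieve IBS-SSS < 175".

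Section 2.11.3 gives the between-arm tests. Student's t-test "will be used to examine differences in all quantitative variables", and the categorical rule is a "chi-squared test for all categorical variables between the two intervention groups (NICE vs. MED-LFD"). No rank or ordinal between-arm test is named. The section adds that "a test-for-trend will be performed to assess any potential longitudinal changes"; this concerns change over time, not an ordered comparison of the two arms.

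**The concern.** A single item with five verbal labels is most naturally a categorical variable, and the rule covers all of them without exception. Adherence would then be compared by a 2×5 Pearson chi-squared test on 4 degrees of freedom. The adherence signal lies in the order of the labels (one arm sitting lower on the scale than the other), and this test does not use that order.

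Adherence bears on how the results are read. The control arm chooses foods freely within categories (2.4.2), whereas the intervention arm follows a strict restriction and then a structured reintroduction (2.4.3), so a one-directional difference is the plausible alternative. Section 2.11.2 also analyses change in IBS-SSS among participants who kept strictly to the protocol. The article does not say that the weekly item decides who they are, but whether the arms adhered equally matters for judging that comparison. A weak test makes it easier to report comparable adherence when it was not comparable.

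**Working it through.** **Plan's own figure.** The protocol states no expected distribution, effect or power for adherence, so there is nothing to reproduce on this point. The 108 participants in 2.11.1 belong to the IBS-SSS outcome; only the 54 per arm is used here.

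**Inputs from the protocol.** Five ordered levels (2.8.3); 54 per arm, alpha 0.05 (2.11.1). Also used: 54 × 0.9 = 48.6, so 49 per arm. Both are shown because the 10% allowance is labelled as being for non-adherence ("significance level α = 0.05, and 10% adjustment for non-adherence"), and removing non-adherers from an adherence comparison is debatable.

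**Assumptions.** Two-sided tests, one value per person, a proportional-odds shift, and assumed baseline distributions.

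**Step 1: order is not used.** X² = Σ(O − E)²/E, summed over the ten cells. Permuting the five columns only reorders the terms, so X² and its p-value do not change.

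**Step 2: analytic cost.** A one-directional signal with 80% power on 1 df has noncentrality (1.96 + 0.8416)² = 7.85. Spreading the same noncentrality over more degrees of freedom gives 70.9% power on 2 df, 64.5% on 3 df and 59.5% on 4 df. The loss from 1 to 4 df is 80 − 59.5 = 20.5 points.

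**Step 3: simulation.** There were 6,000 trials per scenario (Monte Carlo standard error of each power at most √(0.25/6000) = 0.65 points). Pearson chi-squared was compared with the tie-corrected Wilcoxon rank-sum test. A shift multiplies each cumulative odds by the odds ratio. For example, baseline 2/5/13/40/40% has cumulative proportions 0.02, 0.07, 0.20, 0.60 and odds 0.0204, 0.0753, 0.25, 1.5. Doubling the odds gives cumulative proportions 0.039, 0.131, 0.333, 0.75, that is 3.9/9.2/20.2/41.7/25%.

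Columns 2 to 4 use that baseline with 54 per arm. Column 5 covers four baselines using all five levels (uniform, centred, and two skewed to high adherence) at 49 and 54 per arm. Column 6 covers a baseline using only the top three levels, at both sizes.

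| Odds ratio | Chi-squared | Rank-sum | Loss (points) | Loss, five levels used | Loss, three levels used |
|---|---|---|---|---|---|
| 1.5 | 10.4% | 20.5% | 10.1 | 7.7–10.1 | 4.0–5.3 |
| 2 | 28.5% | 49.6% | 21.1 | 19.0–21.6 | 8.8–10.0 |
| 2.5 | 50.2% | 73.8% | 23.6 | 21.5–24.2 | 10.9–11.1 |
| 3 | 68.2% | 87.3% | 19.2 | 17.4–21.9 | 8.5–9.8 |
| 4 | 88.4% | 97.2% | 8.8 | 7.2–11.9 | 3.5–5.4 |

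(The loss at odds ratio 3 is from unrounded powers.)

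**Step 4: where the loss disappears or reverses.**
- If the labels are scored 1 to 5 and t-tested (49 per arm, four assumed distributions, odds ratios 2, 2.5 and 3, 3,000 trials each), power is within 0 to 2.5 points of the rank test: for example 45.3% against 46.2% at odds ratio 2, and 83.6% against 84.0% at odds ratio 3.
- If the difference is not one-directional, chi-squared is better. For 2/5/13/40/40% against 2/15/13/20/50% with 54 per arm, chi-squared has 54.5% power and the rank test 5.9%. Over four such patterns the rank test is 47 to 56 points worse.

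**Step 5: sparse cells.** With 49 per arm and three non-uniform baselines, at least one expected count fell below 5 in more than 96% of simulated trials. The chi-squared type I error over the four baselines of that run (those three and a uniform one) was 3.6 to 4.7%, slightly below the nominal 5%.

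**The case against.** The strongest reply is that the protocol never assigns adherence to chi-squared. The item is described as a scored Likert scale, and the other Likert instruments become numeric scores (IBS-QoL in Appendix B.3, GSRS-IBS in Appendix B.4). Scored in the same way, adherence would go to the t-test and almost nothing would be lost. Weekly ratings must also be reduced to one value first, and that step decides the variable type: a mean score leads to the t-test, and an adherent yes/no to a 2×2 table where order is not at issue. A summary rule may sit in an analysis plan that is not shown.

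Much of this stands. The assignment to chi-squared is an inference, and the absence of a summary rule is not itself a fault. But Appendices B.3 and B.4 number their response options and say how they are transformed or averaged, while 2.8.3 gives only verbal labels. The categorical reading is therefore the more natural one, though not the only one.

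It is also fair to say that the rank test is no cure at this sample size. At odds ratio 2 it too would miss the difference about half the time. The relative frequencies promised in 2.11.3 would still show a shift, and a subgroup of 40 has dietary recalls (2.12).

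**Conclusion.** The point holds in a limited form. The stated rule, read naturally, applies an unordered test to an ordered secondary endpoint. If adherence shifts in one direction under proportional odds, with 49 to 54 per arm and one value per person, the loss of power is about 8 to 10 points at an odds ratio of 1.5, about 17 to 24 at 2 to 3, and about 3.5 to 11 if only three levels are used.

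Three stronger conclusions that a reader might draw are not supported:
- That the trial will lose a fixed 20 points or so. The documents give no adherence distribution or effect; that size belongs to moderate shifts with all five levels in use, and the sign reverses for non-monotone differences.
- That sparse cells make the chi-squared test invalid. In simulation it was only mildly conservative.
- That the efficacy result is compromised. Adherence is a secondary endpoint, and no test of the primary endpoint depends on this choice.

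The change is worth making because it costs almost nothing, not because the harm is large.

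**What to change.** In 2.11.3, exempt the adherence scale from the chi-squared rule. Suggested wording: 'Each participant's weekly adherence ratings will be reduced to one value, the median over a window common to both arms, and compared between arms with the Wilcoxon rank-sum test (or proportional-odds regression).'

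The common window matters because the first follow-up falls at different times in the two arms (2.9). One value per participant matters because pooled weekly answers are not independent. With an even number of weeks the median can fall between two labels. The rank test handles this, but a proportional-odds model needs a stated convention.

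The cost is one sentence, with no new data, visits or participants, plus less sensitivity to non-monotone differences. Tabulating the five frequencies by arm, as 2.11.3 already implies, keeps such patterns visible.

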### 2.12. Exploratory Analyses

Aiming to explore the physiology mechanism implicated in the development of the positive effects of the MED-LFD in IBS symptoms management, we foresee the following mechanistic exploratory analyses in a subgroup of 40 participants (20 from each intervention group) who will provide stool samples at each study timepoint for gut microbiota analysis using metagenomics, and short-chain fatty acids (SCFAs)—acetate, butyrate, and propionate—the intestinal bacterial metabolites produced by fermented nondigestible carbohydrates [11], measurement using Gas Chromatography/Mass Spectrometry. In this subgroup, detailed measurements of the adherence to the diet will be assessed with three-day 24 h dietary recalls (on consecutive days, including a weekend day) twice by telephone contact. The first one at two weeks after interventions started, and the second six months after interventions started for both groups. The dietary recalls aim to calculate the number of consumed FODMAPs per day.

#### 2.12.1. Fecal Samples Collection

Following signing specific informed consent, participants will be asked to provide a stool sample at three different timepoints: baseline, first follow-up, and second follow-up. The stool samples will be immediately frozen after collection and stored at −80 °C in 2 mL screw cap cryovials until further analyses.

#### 2.12.2. Metagenomic Analysis

The analysis will be undertaken to evaluate the effects (immediate and long term) of the two diets on the participants’ microbiome. The exact protocol for the metagenomic analysis is shown in Appendix C.

#### 2.12.3. Short-Chain Fatty Acids Measurements

Using Gas Chromatography/Mass Spectrometry (GC/MS), gaseous eluted compounds like the short-chain fatty acids in the stool are ionized, their ions are separated based on their mass-to-charge ratios, and the intensity of each ion is measured [40]. We aim to investigate the changes in the fecal short-chain fatty acids intensity (immediate and long term) and to compare them between the two IBS groups. The exact protocol for the GC/MS analysis is shown in Appendix D.

## 3. Expected Results and Discussion

During the last two decades, campaigns initiated by impact journals have advocated for access to original trial data, including the case record forms [41]. Sharing clinical study protocols can significantly enhance the caliber of research through various means: It permits researchers to receive input on their protocols via peer review, although studies with ethical approval or funding often receive feedback on initial drafts. However, even the most meticulously planned study might encounter challenges defending contentious elements in its protocol. Moreover, the publication of protocols facilitates comparisons between the original intentions and the actual execution, crucial for preventing data manipulation or selective reporting. Making study protocols public helps researchers comprehend ongoing studies, curbing redundant research efforts. It also assists systematic reviewers in identifying trials, potentially mitigating publication bias. Lastly, the disclosure of study protocols allows participants to identify studies they might consider participating in, empowering their decision-making process [42].

We present herein our single-center, randomized controlled study to evaluate the clinical effects of the LFD combined with the elements of the MΕD in comparison to the dietetic consultations of the NICE for the management of IBS symptoms. Additionally, we foresee the conduction of two physiology studies aiming to better understand the clinical results of the study.

Chen et al. found that while standard MΕD was not associated with the severity of the disease, certain MED foods were linked to symptoms indicating personalized management for those with severe symptoms [13]. Paduano et al. concluded that MΕD is well-accepted and easier to follow than other proposed diets for short-term periods (4 weeks), while they did not find evidence of LFD superiority against MED in improving the quality of life of IBS participants [14]. Moreover, a diet that excludes nutrient-rich foods can lead to nutritional inadequacy. Introducing LFD for a long period can result in insufficient intake of essential nutrients like carbohydrates, fiber, iron, folate, magnesium, vitamin C, B vitamins, and calcium [43,44,45].

According to NICE guidelines, specific lifestyle changes may improve IBS symptoms. It is important to note that FODMAP-containing foods are not specifically restricted in the guidance, but it may be helpful to limit the intake of high-fiber foods [46]. The same dietary advice is followed in the restrictive phase of LFD where fiber consumption is restricted [3,43]. However, dietary fiber increases the levels of SCFAs such as acetate, propionate, and butyrate in the colon through gut microbial fermentation [47], which pose anti-inflammatory properties, enhance the immune response, and contribute to gut barrier integrity. SCFAs have been proven to improve gut health through several local effects, such as maintaining intestinal barrier integrity, mucus production, and protection against inflammation, as well as reducing the risk of colorectal cancer [48]. Despite the challenging nature of IBS, diet and dietary end-products are linked to both the development and management of the syndrome. While most of the literature focuses on SCFAs, research on how BCFAs influence the dietary management of IBS is limited. Nevertheless, LFD is an established dietary intervention that has been found to alleviate IBS symptoms. It leads to higher protein and amino acid fermentation, and, as a result, may produce BCFAs, the byproduct of this fermentation. Despite the protective role that BCFAs might play in gut inflammation [11], other nitrogenous metabolites of protein fermentation, such as amines, hydrogen sulfide, p-cresol, phenols, and ammonia, have been found to have detrimental effects on colonocytes and are associated with gut inflammation, a condition that has been pathogenetically linked with IBS, and consequently with quality of life. In addition, reduced diversity of the gut microbiota and the presence of *Clostridiales*, *Prevotella*, and methanogenic species were proposed as an IBS-specific microbiome signature that is associated with the severity of symptoms [49]. These properties are essential for IBS, which is characterized by increased intestinal permeability, intestinal dysbiosis, and low-grade inflammation [11,50].

According to our study protocol, both groups are expected to consume an average of 25 g of fiber daily. While the literature provides insufficient data to determine the optimal dosage or duration of fiber consumption, the American Academy of Nutrition and Dietetics recommends a daily fiber intake of 25 g for women and 38 g for men, which can benefit IBS participants of all subtypes and improve overall well-being [51].

This trial introduces a new dietary pattern that combines the LFD and the MED to manage IBS symptoms. The innovative aspect of this approach lies in the synergistic action of both diets, with the MED’s anti-inflammatory and prebiotic properties enhancing the effects of the LFD while minimizing its limitations. We believe that enriching the LFD with the components of the MED will effectively optimize its benefits and alleviate the symptoms of IBS. Moreover, the two exploratory analyses are expected to provide physiological grounds to explain the clinical results.

Our study protocol has limitations. One of these is the lack of blinding; this will affect the clinical response to some extent. Additionally, we are unable to examine the effects of systematically altering dietary fiber intake in IBS patients because we do not differentiate between soluble and insoluble dietary fibers. A serious limitation for a trial that wishes to prove the advantages of a Mediterranean pattern compared to the comparator is that both groups will have similar access to extra virgin olive oil intake—the primary source of fat in Greek cuisine—and its anti-inflammatory properties benefitting the entire IBS cohort [51]. Another limitation is that some methodologies appear resource-intensive, involving sophisticated equipment and specialized reagents (e.g., Nanopore, GC/MS). Although such resource requirements could pose challenges for replication and broader implementation in settings with limited access to these resources, these are referred to as exploratory analyses to understand more clearly the pathophysiology dietary manipulation on microbiota and on BCFAs/SCFAs production in IBS. While potential changes in gut microbiota composition may be notable, a critical assessment requires considering various factors such as study design, context, causality, functional implications, and the complexity of the gut microbial ecosystem. Further research and a nuanced approach might be necessary to draw meaningful conclusions about the implications of these microbiota changes in different health conditions.

